The aim of the current paper is to describe our research design. Our primary objective is to evaluate the efficacy of MBI on depressive symptoms of MS patients, compared to an active control intervention, and to assess whether these expected benefits can be maintained at the 6-month follow-up. Secondary aims of the study are: to assess whether after the Mindfulness Based Intervention there is an improvement in QoL, anxiety, fatigue and perceived stress levels; to evaluate the efficacy of the intervention on the perception of the illness and whether participating in MBI also improve interpersonal relationships; to evaluate the efficacy of MBI on depression, QoL and related symptoms in caregivers.

We hypothesize that MBI intervention will lead to a reduction of depressive symptoms, and its associated symptoms both at a physical and psychological levels, compared to an active control group.

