#### Outcome measures and statistical analysis

Primary outcome measures will be: 1) the improvements of BDI-II score from T0 to T2; 2) the proportion of participants at T2 that do not have a BDI-II score greater than 13.

Secondary outcome measures will be the comparison of the scores of FAMS, BAI, FSS, IIP, IPQ-Brief, PSS, PTGI and FFMQ of the two groups at T0, T1 and T2. Another secondary outcome aim will be the reduction of psychological symptoms (BDI-II, BAI, IIP, PSS, PTGI) and a reduction in QoL (WHOQoL-Brief) in caregivers of patients with MS.

The efficacy of MBI will be evaluated by comparing the results to different instruments administered to patients before participating at MBI (T0), after MBI (T1) and at the 6-month follow-up (T2) and by comparing these results with those of patients who were included in the active control group. Intention to treat analyses will be used.

A longitudinal (within subjects) and cross sectional (between subjects) evaluation of our outcome measures will be performed through a repeated measures multivariate analysis of covariance (ANCOVA) using the SPSS GLM procedure. The pre-treatment value will be the covariate, and the treatment condition will be the inter-subjects factor. The intra-subject factor will be a time condition, relating to changes from post-treatment to 6-month follow-up.

The proportion of participants at T1 and T2 no longer meeting the BDI-II cut-off criteria for depression will be evaluated through the Chi square test.

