#### Power calculation

The sample size calculation is based on the primary outcomes for patients with MS.

Statistical power calculation was based on previous studies [28, 48]: assuming power =0.80 and 0.05 significance, a minimal sample size of 44 patients/group will be required, based on an effect size of 0.54.

To obtain the 88 patients needed for the study, it is expected to do the screening of at least 600 patients. On the basis of the information that is available on the prevalence of depression in MS patients, on the average 25 % in previous studies, this number should guarantee there will be at least 150 participants. The number of refusals and treatment interruptions is estimated at not above 40 % which leads to about 90 cases.

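### The stated repeated-measures ANCOVA names neither the BDI-II arm difference at 6 months nor its loss since the end of treatment, so a non-significant change could be mistaken for maintained benefit.

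*Protocol article*

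**What the plan says.** All references are to the protocol article.

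- **Objective** (Background, final part). Besides efficacy against the active control, the primary objective is "to assess whether these expected benefits can be maintained at the 6-month follow-up".
- **Primary outcomes** (Outcome measures and statistical analysis). Both are set at T2: "the improvements of BDI-II score from T0 to T2" and "the proportion of participants at T2 that do not have a BDI-II score greater than 13".
- **Comparison** (same section). Results at T0, T1 and T2 are to be judged "by comparing these results with those of patients who were included in the active control group".
- **Model for scores** (same section). A repeated-measures ANCOVA in SPSS GLM: "The pre-treatment value will be the covariate, and the treatment condition will be the inter-subjects factor". On time: "The intra-subject factor will be a time condition, relating to changes from post-treatment to 6-month follow-up".
- **Binary analysis** (same section). "The proportion of participants at T1 and T2 no longer meeting the BDI-II cut-off criteria for depression will be evaluated through the Chi square test".
- **Size** (Power calculation). "assuming power =0.80 and 0.05 significance, a minimal sample size of 44 patients/group will be required, based on an effect size of 0.54".

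The article gives no criterion for calling a benefit maintained and names no arm contrast at T2 for the continuous score.

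**The concern.** Benefit here means MBI against active control. Whether it is maintained therefore depends on two quantities: the arm difference at T2, and how much that difference has moved since T1. The two effects that the model description names supply neither.

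- The treatment effect, with T1 and T2 as the two repeated levels, is the arm difference averaged over both visits. A large difference at T1 can carry it even if little is left at T2.
- The time effect compares T2 with T1 over both arms together. If MBI patients worsen and controls improve by the same amount, it is zero although the benefit has shrunk.

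The time-by-treatment term, which the design implies but the text does not name, does address loss of benefit. It is a test for change, however, and failing to reject it does not show that little was lost. At stake is the 6-month half of the primary objective: a significant treatment effect with no significant change could be reported as a lasting benefit when half of it has gone.

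**Working it through.** **Inputs from the protocol.** 44 per arm, effect size 0.54, significance 0.05, power 0.80 (Power calculation); 1:1 allocation (Randomization and blinding).

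**Assumptions.** The true arm difference is 0.54 SD at T1 and 0.27 SD at T2 (half lost). SDs are equal at both visits and in both arms, in units of the SD to which the 0.54 refers. There is no loss to follow-up and tests are two-sided at 5%. The correlation r between T1 and T2 is not in the protocol, so it is ranged.

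**The plan's own figure.** A two-sample t test at d = 0.54 needs 44 per arm for 80% power if one-sided at 0.05 (power 0.807), and 55 if two-sided (44 per arm gives 0.71). The protocol does not state sidedness. The stated 44 is used below as it stands.

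**Step 1: power to detect the loss.** With two repeated levels, the time-by-treatment test is a two-sample comparison of T2 − T1.

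- SD of change = √(2(1 − r)); SE = SD × √(2/44); noncentrality = 0.27/SE; 86 df.
- Example, r = 0.5: SD = 1.000, SE = 0.213, noncentrality = 1.27, power 0.24.
- Example, r = 0.8: SD = 0.632, SE = 0.135, noncentrality = 2.00, power 0.51.

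**Step 2: the averaged treatment effect.** Its true value is (0.54 + 0.27)/2 = 0.405 SD, and the SD of a patient's two-visit mean is √((1 + r)/2). At r = 0.5, SE = 0.866 × √(2/44) = 0.185, noncentrality = 2.19 and power 0.58. At r = 0.8, SE = 0.202, noncentrality = 2.00 and power 0.51.

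**Step 3: both together.** With equal variances the mean and the difference of the two visits are uncorrelated, so the chance of a significant averaged effect with a non-significant change is close to the product. At r = 0.5 this is 0.76 × 0.583 = 0.44; at r = 0.8 it is 0.492 × 0.508 = 0.25. Simulation of patient-level data (200,000 trials) gives the same values, and also gives the last column.

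| r | Power for half loss | Change not significant | Averaged effect significant, change not | T2 difference significant, change not | 95% CI half-width for change in arm difference (SD) |
|---|---|---|---|---|---|
| 0.5 | 24% | 76% | 44% | 22% | 0.42 |
| 0.7 | 37% | 63% | 34% | 20% | 0.33 |
| 0.8 | 51% | 49% | 25% | 16% | 0.27 |
| 0.9 | 80% | 20% | 10% | 7% | 0.19 |

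(The fifth column is from the simulation; the half-width is 1.99 × SE.)

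**Step 4: would a formal margin be feasible?** For illustration, take a margin of 0.27 SD, one-sided 0.025, 80% power and no true loss: n per arm = 2 × (1.96 + 0.84)² × 2(1 − r)/0.27². This is 216 (r = 0.5), 130 (r = 0.7), 87 (r = 0.8) and 44 (r = 0.9), against 44 planned.

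**The case against.** The strongest reply is that the protocol already answers the 6-month question by superiority. Both primary outcomes are at T2, results are compared with the active control at every visit, and the chi-square test is applied at T2. On a plain reading, maintained means still present at 6 months, and for that question less informative data make success harder. This stands for primary outcome 2. For continuous BDI-II it stands as intention only, because the model described for that outcome does not name the T2 contrast, and its treatment effect is not that contrast.

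A reader might infer that the authors set out to prove maintenance and will take non-significance as proof. The text does not support this. The objective is to assess whether benefit lasts, and no decision rule is stated. A reader might also take the 49% to 76% of non-significant change tests as the rate of false claims of maintenance. That ignores whether any treatment effect is shown at the same time; the joint figures are smaller, and smaller again once the T2 difference must be significant.

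It is also fair that an interpretation rule or margin may sit in an analysis plan that is not shown. The absence of a margin is therefore not held against the article. What remains is the model that the article does describe, which does not match its own primary outcome 1 and objective.

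**Conclusion.** The point holds as a mismatch between the objective and primary outcome 1 on one side and the stated model for BDI-II on the other. Followed literally, the model reports an average over T1 and T2 and a test for change. It names neither the T2 arm difference nor the loss since T1.

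If half of the benefit were lost, the interaction test would more often than not miss it at r = 0.5 to 0.7, and would miss it about half the time at r = 0.8. The misleading pattern of a significant averaged effect with no significant change would occur in about 44% to 25% of trials for r = 0.5 to 0.8. Requiring a significant T2 contrast would bring this down to about 22% to 16%. These figures rest on the assumed correlation, equal SDs and complete data, and at r = 0.9 the problem is small. The change is worth making because it protects a conclusion on the primary objective. It does not call for a redesign.

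**What to change.** In Outcome measures and statistical analysis, add that the following will be reported from the same repeated-measures model, with the time-by-treatment term included:

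1. the baseline-adjusted MBI-minus-control difference in BDI-II at T2, with 95% CI, as the analysis of primary outcome 1;
2. the change in that difference from T1 to T2, with 95% CI.

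State also that maintenance will not be inferred from a non-significant time or time-by-treatment test. If the interval in (2) is wide, the conclusion is limited to whether a benefit is present, or not shown, at 6 months.

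No formal loss margin is asked for. At 0.27 SD it would need about 87 to 216 per arm for r = 0.8 to 0.5, which 88 patients in total cannot supply.

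The cost is a few sentences, with no new data or visits. The downside is that the word maintained becomes harder to claim with this sample: at r = 0.5 to 0.8 the interval in (2) extends 0.42 to 0.27 SD either side, which is half or more of the planned effect.

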#### Power calculation

The sample size calculation is based on the primary outcomes for patients with MS.

Statistical power calculation was based on previous studies [28, 48]: assuming power =0.80 and 0.05 significance, a minimal sample size of 44 patients/group will be required, based on an effect size of 0.54.

To obtain the 88 patients needed for the study, it is expected to do the screening of at least 600 patients. On the basis of the information that is available on the prevalence of depression in MS patients, on the average 25 % in previous studies, this number should guarantee there will be at least 150 participants. The number of refusals and treatment interruptions is estimated at not above 40 % which leads to about 90 cases.

## Discussion

As far as we know this trial will be the first randomized controlled trial testing the efficacy of group-based MBI for patients with MS with a comparison with an active control group with a specific focus on depressive symptoms.

Secondary outcome measures are levels of QoL, anxiety, perceived stress quality of interpersonal relationship, illness perception and fatigue.

The main strengths of this trial are: 1) a comparison with an active control group; 2) a main focus on depressive symptoms; 3) psychological symptoms are not only self-reported but our assessment includes also a clinical interview; 4) involvement and assessment of caregivers’ psychosocial functioning.

The comparison with an active control group, that is specifically designed to control for the non-specific elements of the MBI treatment and matched for duration and format of group, will permit to assess with an adequate methodology the role of mindfulness training on changes in several psychosocial and physical measures.

The focus on depressive symptoms is supported from what is stated by the Goldman Consensus Conference [12] and by the American Academy of Neurology [13] that highlight how depression is under-diagnosed and under-treated in people with MS and can lead to a decrease in adherence to medication as well as a reduced QoL. MBIs have been proven effective in improving depressive symptoms and in enhancing QoL in many different chronic conditions and recently also in patients with MS. MBIs can therefore be useful in counteracting the suffering caused by the symptoms, the fatigue, the depressive and anxiety symptomatology and the distress in dealing with the disability.

Previous studies did not use objective measures of psychosocial functioning of patients before and after the intervention, and their findings were based only upon outcome measures reported by patients. In this study we propose to assess patients’ psychological functioning with a semi-structured clinical interview (SCID) in addition to the self-reported measures.

Furthermore, our project aims to involve patients’ caregivers. We expect that caregivers will benefit from the treatment received, taking into consideration the load of stress and difficulties related to the management of a chronic disabling diseases like MS. In fact, a recent study has shown that patients’ depressive state influences the deterioration of QoL and the depression of caregivers [49].

Finally, our project is based on MBSR and MBCT protocols, but in order to maximize the clinical utility in people suffering from MS and depression we tailored mindfulness intervention on the needs of this specific population [44]. We will apply a modified MBSR protocol integrated with body centered techniques from Sensorimotor Psychotherapy [45]. SP was developed by Pat Ogden on the model of Ron Kurtz, a body psychotherapy built on mindfulness [50]. Most of these points are already part of the MBSR and MBCT model, but in this integration they are deepened more specifically to increase clinical efficacy.

Results of this trial will provide methodologically grounded data to consider the applicability of MBIs in the usual practice of MS care centers and can help to broad treatment possibilities for patients with MS-related psychological distress.

This study has some potential limitations. The main limitation of the project is the exclusion of patients with a severe disability due to the characteristics of the intervention, which requires a mobility at least partially preserved. In addition, no neuroimaging and neurobiological assessments are planned in the project.

Still and in conclusion, we deem that this study may be the first clinical controlled trial in which MBI will be investigated in comparison with an active control group in patients with MS.

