### Intervention

Treatments will be independent and blinded from the clinical psychologists conducting the clinical assessments. The experimental group will undergo a 8 weekly sessions of 3 h each with a group based Mindfulness Based Intervention. The control group will follow the same structure as the Mindfulness Based Intervention.

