#### Mindfulness based intervention (MBI)

The MBI is based on Mindfulness Based Stress Reduction (MBSR) [42] and Mindfulness Based Cognitive Therapy (MBCT [43] protocols. The MBI comprises an 8-week group program. Participants will took part in a 3 h single weekly sessions, and there will be also an additional all-day session of 7 h. Each session will cover specific exercises and topics within the context of mindfulness practice and training (body scan, breath meditation, walking meditation, yoga exercises). Participants will be required to carry out daily 45-min homework assignments, which consist on mindfulness exercises and mindfulness applications in everyday life. We will attempt to objectively verify the execution of homework practice through the clinical diary.

In order to maximize the clinical utility in people with MS suffering from depressive symptoms, we will tailor mindfulness intervention on the needs of this specific population [44].

We will apply a modified MBSR protocol integrated with techniques from Sensorimotor Psychotherapy (SP) [45], in which:particular emphasis will be paid to somatic resources (grounding, centering, boundaries, lengthening the spine, body self-soothing techniques, etc.) to stabilize the emotional state to prepare and sustain the mindful disposition;explanation of stress response will be integrated with the concept of “window of tolerance” [46], that is the range of optimal arousal which is necessary to stay in touch with the present moment experience. This concept allows a more precise awareness of the arousal state, recognizing hyper-arousal and hypo-arousal symptoms, and consequently to manage them more effectively;considering the attention deficits, which may be due both to neuropsychological deficits and to the depression itself, great attention is paid to attention training;considering interpersonal deficits in depression, interpersonal mindful listening is specifically addressed, developing the capacity to listen in a mindful state, creating a space inside to observe in a compassionate and non-judgmental way sensations, emotions and thoughts evoked by the other’s narration;great treatment emphasis will be paid on acceptance and self-compassion, and specific tools are used to increase it, such assessment and decentering of negative cognitions, and mindful body self- touch, becoming aware of sensations, feelings, thoughts and needs in the intimate relationship with the self.

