#### Active control group

Our control group is based on the active control group of the study of Grossman et al. [47].

This intervention was designed to control for the non-specific elements of the MBI treatment. It will be based on a psycho-educational framework and will include some relaxation techniques.

In each session is discussed a MS-related topic. Relaxation and gentle stretching exercises will be proposed at the end of each session. Homework and the material (photocopies, slides, etc.) discussed in group sessions is left to each participant to encourage participants to practice exercises between sessions. This intervention will follow the same structure and weekly format of the MBI intervention. The only difference will be the absence of an all-day session. Each component has its counterpart in the MBI curriculum, but emphasis is placed upon not describing or training mindfulness skills to the control group. The groups will be delivered by a psychotherapist with relaxation training experience, who is experienced in working with people with MS.

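### The Discussion calls the active control matched for duration, but the planned schedule gives MBI 31 h of group contact against 24 h, so a difference cannot be credited to mindfulness training alone

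*Protocol article*

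**What the plan says.** Four places in the protocol article bear on this.

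- **Intervention** sets the schedule: "The experimental group will undergo a 8 weekly sessions of 3 h each with a group based Mindfulness Based Intervention". It then says of the comparator: "The control group will follow the same structure as the Mindfulness Based Intervention".
- **Mindfulness based intervention (MBI)** adds to that schedule: "there will be also an additional all-day session of 7 h". On home practice it says: "Participants will be required to carry out daily 45-min homework assignments".
- **Active control group** says: "This intervention will follow the same structure and weekly format of the MBI intervention". It continues: "The only difference will be the absence of an all-day session". It also says that homework and session material are given to participants to encourage practice, and that every component has a counterpart in the MBI programme. It states no amount of homework.
- **Discussion** presents the comparator as one "that is specifically designed to control for the non-specific elements of the MBI treatment and matched for duration and format of group", and concludes that this allows the role of mindfulness training to be assessed. The limitations at the end of the Discussion mention the exclusion of severely disabled patients and the lack of neuroimaging and neurobiological measures. They do not mention unequal contact time.

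**The concern.** The Active control group section says the comparator exists to control for the non-specific elements of MBI. Time with a therapist and time in a group are such elements. The Discussion says they are matched in duration and draws a specific inference from that: a difference between arms speaks to mindfulness training as such. If planned contact is unequal, the inference does not follow, because part of any BDI-II difference could come from the additional contact.

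What is at stake is the interpretation of a positive result, not the test. Someone who reads only the Discussion would take the arms as equal in time and would find nothing among the limitations to correct that impression.

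**Working it through.** The article states no total of contact hours, so there is no figure to reproduce. The totals follow from the schedule.

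**Inputs**

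- Weekly sessions, MBI: 8 sessions of 3 h (Intervention).
- All-day session, MBI: 7 h (Mindfulness based intervention).
- Weekly sessions, control: the same weekly format as MBI (Active control group), read here as 8 sessions of 3 h.
- All-day session, control: none (Active control group).

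**Group contact** = sessions × hours per session + all-day session

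| Arm | Calculation | Planned contact |
|---|---|---|
| MBI | 8 × 3 + 7 | 31 h |
| Control | 8 × 3 + 0 | 24 h |

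Difference: 31 − 24 = 7 h. Relative to control: 7 / 24 = 0.29, so MBI has 29% more planned contact. The arms match in number and length of weekly sessions but not in total contact time.

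**Homework**

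MBI requires 45 min (0.75 h) a day. The number of practice days is not given, so the total is a range under assumption:

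- 6 days a week for 8 weeks: 48 × 0.75 = 36 h
- every day for 8 weeks: 56 × 0.75 = 42 h

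The control has homework, but neither an amount nor a requirement is stated, so no between-arm difference can be calculated. Three statements in the article point towards similar homework: the all-day session is called the only difference, each component is said to have a counterpart, and the homework diary in the Assessments section is listed for patients without restriction to one arm. The contrast between required daily practice and encouraged practice points the other way. The text does not settle it.

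**The case against.** The strongest reply is that nothing is concealed. The Active control group section says openly that the all-day session is absent, and the MBI section gives its length. The line about the same structure in the Intervention section is a summary that the later section qualifies. On this view, matching on duration means the same number of weeks, the same weekly session length and the same group format, all of which hold.

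Much of this stands. The gap is disclosed, and the weekly format is matched. But the Discussion uses the match to isolate mindfulness training, and that inference needs the total amount of therapist and group time to be comparable. Disclosure in the Methods confirms that the Discussion sentence is inaccurate as written.

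A reader might be tempted to infer more than the article supports:

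- **That the control has no homework, or that a homework imbalance of 36 to 42 h is established.** The control does have homework, of unstated amount, and a condensed article may leave that amount to the full protocol. MBI homework also consists of mindfulness exercises and applications, so it is at least partly specific content rather than a purely non-specific element.
- **That the trial's claim to novelty falls.** Novelty is claimed for using an active control group with a focus on depressive symptoms, not for equal hours.
- **That no effect could be attributed to MBI at all.** The stated objective and the analysis compare MBI with the active control. Randomization keeps that comparison of packages valid whatever the contact hours.

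**Conclusion.** The point holds in a limited form. The Discussion claims a property, equal duration, that the schedule in the Methods does not have: 31 h against 24 h, a gap of 7 h or 29%. A BDI-II difference could not be attributed to mindfulness training alone; it would reflect MBI as delivered against a control package with less contact. The objective, the primary analysis and the sample size are not affected.

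This rests on reading the control's weekly format as eight 3 h sessions, which the article implies but does not spell out in hours. A homework imbalance is possible but not established. If homework is in fact equal, the 7 h gap remains. The article gives no relation between contact hours and BDI-II, so the share of any effect due to the extra contact cannot be estimated, and no size is claimed for it.

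**What to change.** 1. Reconcile the Intervention, MBI, Active control group and Discussion sections so that planned contact hours and homework for each arm are stated once and agree. This is a request for consistency; it does not say what either schedule should be.
2. Unless both are equal, replace the duration claim in the Discussion with a statement that the arms are matched for number and length of weekly sessions, but not for the 7 h all-day session. Word any homework difference that the reconciliation confirms in the same way.
3. Add the unequal contact time to the limitations in the Discussion.
4. Confine the planned conclusion to MBI as delivered versus the control package.
5. Optionally, report attended hours and diary-recorded home practice by arm as descriptive data. The Assessments section already provides for a diary of homework frequency and duration. This is a reporting choice, not a defect to be repaired.

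The cost is a few sentences and, if item 5 is adopted, one descriptive table. The downside is a slightly weaker claim.
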